### ***Health Economic analysis***

The health economic analyses will investigate differences in treatment costs, as well as indirect costs related to work (dis)ability and sick-leave. The cost-utility analysis will be performed according to well-established methods, taking into account the direct (pre- and post-operative interventions) costs and quality of life (generated from EQ-5D). performed estimating costs per quality-adjusted life year (QALY).

### ***Compliance***

Regular supervision will be conducted with the therapists conducting the pre-operative hypnosis in order to secure compliance to the protocol. The PI and co-PI of the study will be in charge of the supervision. They are both experienced psychologists with a clinical specialization and they are certified in this particular hypnosis intervention. In order to assess compliance with the post-operative intervention, we will have user statistics logged on the web-page i.e. what videos have been used, by which ID and when. This will be used in combination with collecting the work-booklets to see whether the patient has performed different tasks related to the videos. If accepted by GDPR standards, we will associate the

booklet with the given video using an unidentified study ID yielding a rate of completion for the post-operative intervention.

---

### ***Confidentiality***

Participant reported outcome measures (PROMs) will be completed electronically using the ViedocMe functionality available in Viedoc. Study staff will create a ViedocMe account for each participant in the participant's Clinic View in Viedoc and provide an unique log-in profile (user name, pin-code, and ViedocMe web-address) for each participant. Participants are to use this information to log in to their personal ViedocMe account. The questionnaires in ViedocMe will only be available for completion for three days prior to their clinical visitations.

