### **Data collection and management**

Self-reported data and biomarker data will be collected pre-surgery (questionnaires, hair and blood), post-surgery upon discharge (brief phone survey), 3-4 weeks after surgery (blood), as well as 3 and 6 months after surgery (only questionnaire data). These time points either align with clinical follow-ups at the outpatient oncology department, or are responded to through an

electronic link in the patients' homes to avoid unnecessary strain on the patient. Patient charts will be used to collect data on surgical procedures and potential complications during/after surgery. This will include information about the duration of the surgery, tumor-related variables, severity of acute post-surgical pain, and other relevant intra-operative variables. Registry data on employment and benefit take-up and medical prescriptions will be obtained from FD-Trygd and the Norwegian Prescription Database (NorPD), respectively. To be able to assess for the effects of the interventions, data from NorPD and FD-Trygd will be obtained from inclusion in the trial until one year follow-up. The NorPD contains data about dispensed drugs in Norway, while FD-Trygd contains social security micro data for research. These data will be obtained retrospectively. The post-operative booklet that the patients receive as part of the iACT will also be collected at 6 months follow-up to assess if the patients used it as intended.

----- INSERT FIGURE 1-----

Survey data will be collected electronically by the use of laptops/smartphones. We will also utilize data from patients' medical records regarding surgical procedures and medical variables, as well as registry data, which will be linked to the survey data. Data from medical records as well as test results from blood samples will be entered directly into Viedoc by our study nurse. All data will be stored on a secure server at the hospital. The hospital already have a system in place for secure collection and storing of sensitive data which will be used.

A detailed plan for data management and sharing will be developed in collaboration with both Oslo University and the University of Oslo that shares the responsibility for data management in this study.

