## ***Implementation***

The project will be administered from the Dept of Psychology, University of Oslo, which has the infrastructure to carry out such a study. Data will however be collected, stored and analyzed at Oslo University Hospital through Videoc which is an established and secure system for data collection, storing and management approved by the hospital. The trial will be run at the hospital in the Department of Breast and Endocrine surgery, which is a department with extensive experience in running clinical trials. Two study nurses will be employed to work in the out-patient department and on the ward with patient recruitment and biomarker assessments. A research assistant will be responsible for practical aspects of the trial as well as administering the follow-up data collection which we will attempt to align with the regular medical follow-ups following surgery to ensure a high response rate. Trained therapists and the PhD-student will be responsible for the pre-surgery hypnosis intervention. They will go through didactic and practical training, and complete supervised practice as part of their training. The hypnosis script is already translated and has been pilot tested in a small sample of breast cancer patients ([name] et al *in progress*). The iACT has been developed under the leadership of the co-PI of the study ([name]), with input from our national and international partners ([name] & [name]), and user representatives. The user representatives will further be invited to participate in a focus group upon the completion of the post-operative intervention to discuss their experiences of the intervention and share any advice for modifications or changes to the interventions or procedures.

In order to disseminate the results to patients, clinicians, policy makers and the public, we are planning to co-host a seminar with the Norwegian Cancer Society for stakeholders and

collaborators to present results from the trial. The Cancer Society will also communicate the research findings through their channels, which are well organized and far reaching.

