## **Analyses**

### ***Sample size and power***

Sample size is estimated for both of the primary outcomes. Previous trials with similar interventions have demonstrated moderate/large effect sizes on pain and fatigue (26, 60). However, compared to these studies, we expect more heterogeneity in our data as our study population will undergo several medical treatments during the trial (e.g. radiotherapy or chemotherapy after surgery). We thus expect a minimum difference of one point on NRS (0-10) and 3 points on FACIT-F (which corresponds to patients reporting being “slightly better”). Based on previous studies, it is expected that the control group scores 5 (SD: 2.4) on NRS at 3 months follow-up (25), and 18 on FACIT-F (26). With power set at 0.80 and two-tailed  $\alpha$  set at .05, the number needed in each group to detect the change in pain is  $n=92$ , and in fatigue  $n=87$ . To account for attrition and loss to follow-up, we plan to include 100 patients in each group.

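### Questionnaires that open only in the three days before a clinic visit leave no open form for a participant with no visit near 3 or 6 months

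*Protocol*

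**What the plan says.** Three sections of the protocol bear on when a participant can fill in a follow-up questionnaire.

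- **Confidentiality** names the system: "Participant reported outcome measures (PROMs) will be completed electronically using the ViedocMe functionality available in Viedoc". It then limits access: "The questionnaires in ViedocMe will only be available for completion for three days prior to their clinical visitations". It mentions no extension, no reopening and no other route.
- **Data collection and management** places the later assessments at "as well as 3 and 6 months after surgery (only questionnaire data"), so no blood or hair sample is taken then. On how they are completed it gives two alternatives. Either the time point coincides with an outpatient oncology visit, or the participant answers by "electronic link in the patients' homes to avoid unnecessary strain on the patient".
- **Implementation** gives a research assistant the task of "administering the follow-up data collection which we will attempt to align with the regular medical follow-ups following surgery to ensure a high response rate".

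Outcome Measures and Statistical analyses make the 3-month NRS pain and FACIT-F scores the primary comparison. On losses, Sample size and power says only: "To account for attrition and loss to follow-up, we plan to include 100 patients in each group". It states no expected response rate.

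**The concern.** The access rule depends on a clinic visit, but the assessment schedule does not guarantee one. If the forms are configured as Confidentiality describes, three things follow:

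1. A participant without a visit near 3 or 6 months is never offered the form.
2. A participant who has a visit but misses the three days before it cannot answer afterwards.
3. A participant who has a visit and answers in time does so on a date set by the visit, which need not be the date 3 or 6 months after surgery.

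At stake are the two primary outcomes. Both are self-reported, and a 3-month score not collected at the time cannot be reconstructed later from charts or registries. The linear mixed models can use incomplete records, but they do not bring the missing 3-month scores back. The 6-month form falls under the same rule, so a participant could lose both follow-up scores for the same reason.

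**Working it through.** **Step 1: set the sections side by side.**

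| Situation at 3 or 6 months | Data collection and management; Implementation | Confidentiality, read literally |
|---|---|---|
| Visit near the time point, answered at home or in clinic in the three days before | Provided for | Form open: no conflict |
| Visit near the time point, three days missed | No provision stated | Form closed: no late answer |
| No visit near the time point, answered by link | Provided for as the alternative to alignment | Form never opens: conflict |

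The first row matters for scope. ViedocMe is reached by web address and log-in, so home completion as such is compatible with the rule. The contradiction is in the third row. That row is not idle, because alignment is only to be attempted and the 3- and 6-month assessments need no sampling visit. The phone survey at discharge is unaffected.

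**Step 2: reproduce the protocol's sample size for pain.** Inputs from Sample size and power: difference 1 point, SD 2.4, two-sided alpha 0.05, power 0.80.

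- Normal approximation: n = 2 × (1.960 + 0.842)² × 2.4² / 1² = 2 × 7.85 × 5.76 ≈ 90.4, so 91 per group.
- t-test: n = 91.4, so 92 per group. This matches the stated 92.

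The stated 87 for fatigue cannot be checked independently, because no FACIT-F SD is given. Solving backwards from a 3-point difference and n = 87 implies an SD of about 7.0.

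**Step 3: find how much loss the plan absorbs.**

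- Pain: 1 − 92/100 = 8%.
- Fatigue: 1 − 87/100 = 13%.

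This margin has to cover every cause of missing 3-month scores, including withdrawal.

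**Step 4: illustrate larger losses.** The loss rates from 15% upward are assumptions; the protocol gives none. Power is from the two-sample t-test, with standardised difference 1/2.4 for pain and 3/7.02 for fatigue (SD back-solved as above).

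| Missing at 3 months | Evaluable per group | Power, pain | Power, fatigue |
|---|---|---|---|
| 0% | 100 | 0.834 | 0.852 |
| 8% (pain margin) | 92 | 0.803 | 0.822 |
| 13% (fatigue margin) | 87 | 0.780 | 0.800 |
| 15% (assumed) | 85 | 0.771 | 0.791 |
| 20% (assumed) | 80 | 0.745 | 0.766 |
| 30% (assumed) | 70 | 0.687 | 0.709 |

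The table takes the protocol's two groups of 100 as given. It shows what a loss would cost, not how much loss the three-day rule would cause.

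**The case against.** The best defence is that the rule is a sentence about access, placed under Confidentiality, and not the assessment schedule. The schedule fixes assessments at 3 and 6 months after surgery. Clinical visitation is not defined, the figure referred to in Data collection and management is not shown in the text at hand and may hold the timetable, and a detailed data management plan is promised. No section says that the 3-month time point lacks a visit, and staff intend to align follow-up with visits.

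Much of this stands, and it limits what can be claimed:

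- A reader might infer that home completion by link conflicts with the rule. It does not, provided there is a visit and the form is completed in the three days before it.
- A reader might infer that missingness and timing would depend on radiotherapy or chemotherapy through visit scheduling, and that the missing-at-random assumption behind the mixed models is therefore undermined. The protocol mentions these treatments only as a source of heterogeneity and does not link them to visit dates. The rule is the same in every arm, and nothing points to differential loss.
- A reader might take the power table as the effect of the rule. The same table would follow from any cause of dropout.

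The defence does not remove the word that restricts opening to the days before a visit. This is a rule the protocol itself states, not a detail left for a later document, and no analysis plan can recover answers from a form that was closed. The missing tolerance around 3 months would not be a finding by itself, since that is often left to the SAP. It matters here only because the stated rule ties completion to the visit.

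**Conclusion.** The concern holds in a limited form. The access rule in Confidentiality, read literally, contradicts the provision for time points answered by link without an aligned clinic follow-up, and it shuts out late answers where a visit does exist. This puts 3-month primary data at avoidable risk, against an allowance of 8% for pain and 13% for fatigue.

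The size of the loss is unknown. It depends on how many participants have no visit near the time point and how many miss the three days, and the protocol gives neither. The figure of 0.745 for pain at 20% missing is an illustration under an assumed rate. The conclusion rests on reading the rule as written and on there being no other opening mechanism in the schedule figure or the planned data management document. Confidence is therefore moderate to good on the contradiction and low on its practical extent. The documents do not support going further to a claim of biased treatment comparisons or of a predicted shortfall in power.

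**What to change.** Reconcile Confidentiality, Data collection and management, and Implementation so that they give one rule for when the follow-up forms are open:

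- Replace the three-day rule, for the 3- and 6-month forms, with a pre-specified opening window counted from the date of surgery. It should apply to every participant, whether or not a visit is scheduled.
- Allow completion at any time within that window, at home or in clinic. The width is for the trial team to justify; from 7 days before to 21 days after the target date is one example.
- Send reminders while the form is open. The research assistant already responsible for follow-up collection can pursue non-responders.
- Record the completion date, so that time since surgery is known for each score.

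Alignment with clinic visits can remain as a convenience, but it should no longer decide whether the form opens.

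The cost is a change of configuration in Viedoc and a sentence or two in the protocol. The downside is a slightly wider spread of completion dates; because the dates are recorded, the spread can be described. It is best done before the first participants reach 3 months, since scores missed under the present rule cannot be recovered.

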## **Discussion**

Breast cancer is the most common form of cancer among women (1), and a majority of women report persistent psychological and physiological symptoms after breast-cancer surgery (3-5). Chronic post-surgical pain and fatigue are the most common sequelae (6, 11) . This is both a major clinical problem, with prevalence rates ranging up to 60% (6) , and a socioeconomic burden on the health care system (62). Studies on preventive interventions are scarce, and those that have been carried out have not been sufficiently replicated.

This study will to our knowledge be the first study to investigate the combined effects of a pre-operative hypnosis intervention and a web-based post-operative ACT intervention in women about to undergo breast cancer surgery. It will also be among the very few attempts worldwide to prevent the incidence of pain and fatigue after breast cancer surgery applying a psychological approach. This study design has several strengths. The outcome measures are valid and reliable, involving both self-report measures, objective registry data, and biomarker

data, and the study will contribute to the need of rigorous clinical trials within this field of research. The project results will be highly relevant to all health care personnel involved in breast cancer care, but also to the larger community of clinicians and researchers within the field of chronic pain and fatigue.

## **Trial Status**

The trial will start recruiting in April 2020.

## **Abbreviations**

ACT: Acceptance and Commitment Therapy

CPSP: Chronic Post-Surgical Pain

EQ-5D: European Quality of Life – 5 Dimensions

QoL: Quality of Life

RCT: Randomized Controlled Trials

TAU: Treatment As Usual

## **Declarations**

### **Acknowledgements**

### **Funding**

The study is funded by the Norwegian Cancer Society. The funding sources do not have any role in the design of the study, data collection, analysis and interpretation of data, or decisions to submit articles for publication.

**Availability of data and materials**

An anonymized dataset will be made available upon request when the main results of the trial are published.

**Authors' contributions**

[name] is the principal investigator of the study, [name] is the co-PI of the study. [name] and [name] drafted the manuscript and revised it for critical intellectual content.

**Competing interests**

All authors declare that they have no competing interests.

**Consent for publication**

Not applicable.

**Ethics approval and consent to participate**

The study will comply with good clinical practice, including the most recent version of the declaration of Helsinki, as well as all relevant rules and regulations of Norway. The study will be submitted to the Regional ethical committee and the Data Protection Officer at Oslo University Hospital as well as the Data Protection Officer at Oslo University for approval. All participants have signed a statement on consent to participate. The right to withdraw from the study at any time without any explanation, and without any consequences for the further treatment at the clinic, will be emphasized.

